## Methods

The study employs a prospective multicentre observational design in two Czech comprehensive stroke centres, enrolling an estimated 3,000 patients over 3 years.

The inclusion criteria include acute neurological deficits with symptoms lasting up to 24 h and NIHSS ≥0 points (National Institutes of Health Stroke Scale) at enrolment.

The exclusion criteria include age < 18 years, previous severe neurological handicap (mRS = 5), contraindications for CT contrast scan or MRI (pregnancy, severe renal failure, allergy to contrast material, or claustrophobia), and patient non-consent. For the trial flow, see the STARD diagram (Figure 1).

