### Monitored parameters

The following data will be collected and evaluated in Table 1.

**Table 1 tab1:** Following data will be collected and evaluated.

Patient history	
Age Sex Comorbidities Long-term medication	Hypertension, diabetes mellitus, heart disease, arrhythmia, hyperlipidemia, mental disorders, cephalgia, migraine, epilepsy, oncological disease, cognitive deficit antithrombotic medication, hormonal anticonception
Hospitalisation data	
Date and time of stroke/stroke mimics Date of hospital admission Hospitalisation, duration	standard, ICU
Systolic/diastolic blood pressure Laboratory parameters-INR, glycemia, Increase in liver tests, kidney failure, drugs in the blood	
Clinical data	
mRS NIHSS Neurological deficit Type of treatment Multimodal brain CT scan on admission Follow-up NCCT Brain MRI results Final diagnosis	Pre-morbid, at discharge on admission, 24 h after the admission to hospital NCCT, CTA, CTP during 24–36 h after the admission in indicated patients stroke, stroke mimics
Follow-up visit	
mRS value Recurrence of symptoms Clinical condition	

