### Stroke protocol

#### Multimodal CT

All patients with acute neurological deficits (stroke, transient ischaemic stroke (TIA), or SM) will undergo neuroimaging diagnostic procedures as per the stroke protocol, i.e., initial multimodal brain CT (NCCT, CTP, and computed tomography angiography (CTA)), followed by follow-up NCCT within 24–36 h.

The basic CTP parameters define perfusion maps, which express the mean transit time, cerebral blood flow, and cerebral blood volume. Currently, the maps defining the so-called maximum time (Tmax) are also essential. The AI software package allows us to determine the extent of irreversible ischaemia (decrease in CBF below 30% of the reference bilateral value) and potentially the tissue that can be rescued, i.e., penumbra (prolongation of Tmax over 6 s).

Type of CT device—CT Force Siemens.

Stroke protocol: Unenhanced brain: 120 kV (CarekV), 300 mAs (CareDose), collimation 128 × 0.6 mm rotation time 0.5 s Recon: slice 0.75 mm, 5 mm, kernel Hr 40.

CTP: 70 kV, 200 mAs, collimation 48×1.2 mm, brain coverage-4D range: 114 mm.

Cycle time 1.5 s exam time 45 s rotation time 0.25 s contrast medium—40 mL intravenous.

CTA: 120 kV (CarekV), 84 mAs (Care Dose), collimation 128 × 0.6 mm.

Recon: slice 0.5 mm, 3 mm, kernel Hr 36, contrast medium—50 mL intravenous.

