#### MRI examination

All patients without a confirmed concordant hypoperfusion or cerebral ischaemia on their previous CT scans will undergo an MRI examination between the third and seventh day after admission to hospital to confirm the diagnosis of SM.

The MRI examination will be performed using the Siemens Prisma, 3.0 T scanner (Siemens, Erlangen, Germany). The imaging protocol includes:localisers;diffusion weighted imaging (DWI) with b-factor values 0, 400, and 800 s/mm2, calculated b-value of 1,000 s/mm2. ST 3.0 mm, GAP 0.6 mm, TR 2900 ms, TE 60 ms, FOV 256 mm, BW 868 Hz/Px, number of slices 40, TA 2:09;reconstructed maps of an apparent diffusion coefficient (ADC maps);3D FLAIR sequence. The examination will be performed in the sagittal plane with 1 mm MPR axial and coronal reconstructions. TR 5500 ms, TE 383 ms, ST 1 mm, number of slices 160, GAP 0, TI 1800 ms, FA T2 Var. deg., BW 751 Hz/Px, TF 220, TA—acquisition time 3:46. Total examination time 6:12+ shimming time.

Follow-up brain MRI will be performed on the following patients as per the stroke protocol:Patients with a negative initial multimodal CT scan.Patients with discordant CTP results, which means that the location of the hypoperfusion does not correspond with the neurological symptoms, or patients with CTP technical artefacts.Patients with a negative follow-up brain NCCT.Patients with an NIHSS score of zero upon admission to the hospital and 24 h after the onset of TIA.

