### Determination of the definitive diagnosis

Two neurologists specialised in treating and diagnosing stroke will confirm the diagnosis independently.

The following patients will be diagnosed with an ischaemic stroke:Patients with a finding of hypodensity corresponding with subacute ischaemia on the initial brain CT examination.Patients with a new subacute ischaemic lesion on the follow-up NCCT scan within 36 h from the onset of the neurological deficit.Patients with an ischaemic brain lesion on their MRI scan within 3–7 days from the onset of the neurological deficit.

The diagnosis of SM will be determined by the following parameters:organic lesion of aetiology other than ischaemic stroke on the NCCT scan,negative CTP, discordant CTP, and negative control brain MRI,two neurologists and two radiologists specialised in treating and diagnosing stroke will confirm the diagnosis of SM independently, considering the correlation of imaging and clinical data (see clinical data checklist). The radiologists will also assess other thresholds during the CTP examination than the classically established ones (e.g., T max less than 6 s). Both stroke consultants will assess the final diagnosis for the whole group with and without knowledge of the CTP result.

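### The stroke criterion times the follow-up NCCT from onset, but the scan is scheduled from admission, so some infarcts seen on schedule meet no listed diagnostic criterion

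*Protocol article*

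**What the plan says.** All references are to the protocol article, Methods.

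- **Entry.** The inclusion criteria admit "acute neurological deficits with symptoms lasting up to 24 h".
- **Follow-up NCCT, schedule.** Table 1 (Monitored parameters) places it "during 24–36 h after the admission". The Multimodal CT section describes the initial multimodal CT as "followed by follow-up NCCT within 24–36 h" and gives no other anchor.
- **Follow-up NCCT, diagnostic rule.** Determination of the definitive diagnosis lists among the ischaemic strokes: "Patients with a new subacute ischaemic lesion on the follow-up NCCT scan within 36 h from the onset of the neurological deficit".
- **MRI, who is scanned.** The MRI examination section says: "All patients without a confirmed concordant hypoperfusion or cerebral ischaemia on their previous CT scans will undergo an MRI examination". A list later in that section adds a negative initial multimodal CT, discordant CTP or CTP artefacts, an NIHSS of zero, and "Patients with a negative follow-up brain NCCT".
- **MRI, schedule.** It takes place "between the third and seventh day after admission to hospital".
- **MRI, diagnostic rule.** The corresponding stroke criterion is "Patients with an ischaemic brain lesion on their MRI scan within 3–7 days from the onset of the neurological deficit".

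The remaining stroke criterion is hypodensity on the initial CT. For stroke mimic (SM), the imaging parameters are an organic lesion of another cause on NCCT, or negative or discordant CTP with a negative control MRI.

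**The concern.** The scan schedule starts its clock at admission and the diagnostic rule starts its clock at onset. Nothing in the article reconciles them. A patient who arrives some hours after onset and is scanned exactly as planned can have a new infarct that the rule, as worded, does not count.

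This matters because the rule is part of the reference standard, and every sensitivity, specificity and predictive value named in the statistical section is measured against it. The patients at risk are not a random subset. They present later, their initial NCCT shows no hypodensity, and their CTP is positive and concordant. The Discussion expects NCCT, CTA and CTP together to outperform NCCT alone or NCCT with CTA, and these are cases in which CTP is right and the initial NCCT is not. Leaving them out would understate what CTP adds over NCCT. Calling them non-stroke would turn correct CTP results into false positives.

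**Working it through.** **Inputs.** D is the delay from onset to admission, 0 to 24 h (inclusion criteria, read as time since onset). S is the time from admission to follow-up NCCT, 24 to 36 h (Table 1). The limit is 36 h from onset (definitive diagnosis). The article states no figure of its own to reproduce here.

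**Step 1: when on-schedule scans fall.** Time from onset is D + S. The earliest is 0 + 24 = 24 h and the latest is 24 + 36 = 60 h.

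**Step 2: which scans meet the limit.** The condition is D + S ≤ 36, so S ≤ 36 − D. The last D hours of the 12 h window are lost. At D = 12 h only a scan at exactly 24 h after admission qualifies. Above 12 h none does. As a share of the window this is max(0, (12 − D)/12):

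| D (h) | Scan window from onset (h) | Share of window within 36 h |
|---|---|---|
| 0 | 24–36 | 100% |
| 3 | 27–39 | 75% |
| 4.5 | 28.5–40.5 | 62.5% |
| 6 | 30–42 | 50% |
| 9 | 33–45 | 25% |
| 12 | 36–48 | 0% |
| 24 | 48–60 | 0% |

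**Step 3: share of all on-schedule scans beyond 36 h.** The article gives no distribution of delay, so this needs assumptions. With scan times uniform over 24–36 h:

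- D uniform over 0–4.5, 0–6, 0–12 or 0–24 h: 19%, 25%, 50% or 75% fall outside. For example, over 0–6 h the mean loss is 3/12 = 25%. Over 0–24 h it is half the patients at a mean loss of 50% and half at 100%, giving 75%.
- D lognormal (log-SD 1, cut at 24 h) with median 2, 3, 4 or 6 h: 25%, 34%, 41% or 52% fall outside.
- If every scan were done at exactly 24 h after admission, only patients with D above 12 h would fail: none for D up to 12 h, and 50% for D uniform over 0–24 h.

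These are shares of scans, not of patients left without a diagnosis.

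**Step 4: who is left without a criterion.** Remove in turn everyone reached by another rule:

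1. Hypodensity on the initial CT: stroke by the first criterion.
2. Negative initial multimodal CT, discordant CTP or CTP artefacts: sent to MRI.
3. Negative follow-up NCCT: sent to MRI.
4. NIHSS zero as the list defines it: sent to MRI.

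What remains is no initial hypodensity, concordant hypoperfusion, and a new infarct on an on-schedule NCCT more than 36 h after onset. The general MRI rule does not reach these patients, because CT has already shown concordant hypoperfusion and ischaemia. They meet none of the three stroke criteria as worded. With concordant CTP and a visible infarct, they meet no SM imaging parameter either.

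**Step 5: the MRI clock.** The latest on-schedule MRI is 7 days after admission, which is up to 7 + 1 = 8 days after onset, against a limit of 7. The excess is at most one day.

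**The case against.** The strongest reply is that the stroke list names patients who will be diagnosed. It does not say that an infarct first seen after 36 h is to be ignored. Two neurologists confirm each diagnosis, and in practice they would probably call such a patient a stroke. That is fair, and it limits the harm. But the article states no such override. If the raters disregard the limit, it serves no purpose in the definition. If they apply it, infarcts are lost. If they differ, classification depends on the rater, and in one of the two planned assessments the raters know the CTP result.

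A second reply is that MRI closes the gap. It does so for the groups removed in step 4 of the working, and this should be conceded in full. It does not reach the group that remains.

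Two alternative readings of the text do not remove the conflict. If the 24 h in the inclusion criteria means symptom duration, the delay is not capped at all. Table 1 is flattened in the text, but its 24–36 h entry fits only the follow-up NCCT.

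A reader might also infer that these strokes end up as SM by default. The documents do not support that, since the SM imaging parameters do not fit them either. Nor does the Introduction say that CTP matters most for diagnosing late presenters. It discusses late and unknown-onset patients in terms of selection for recanalisation, and adds that this role has declined.

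**Conclusion.** The concern holds as an inconsistency between the scan schedule and the reference standard. That on-schedule scans fall 24–60 h after onset, and that none meets the limit once the delay exceeds 12 h, follows from the stated windows alone and needs no assumed distribution. The consequence is confined to one subgroup: no initial hypodensity, concordant CTP, and a new infarct on an NCCT beyond 36 h from onset. Read literally, these patients are unclassifiable.

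The number affected cannot be derived from the document. It is tempting to read the 19–75% range as the share of patients misclassified. It is not: it counts all on-schedule scans under assumed delays, including scans of patients with SM, patients already classified by the initial CT and patients sent to MRI. The affected share must be smaller. The subgroup still bears directly on the comparison of CTP with NCCT, so excluding it or classifying it inconsistently would bias that comparison. The MRI mismatch is minor. This should be fixed; it does not put the study as a whole in doubt.

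**What to change.** Use one time origin in the reference-standard definition, and reconcile Table 1, the MRI examination section and Determination of the definitive diagnosis to it. The simplest form lets a lesion on any protocol-scheduled follow-up scan count:

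- NCCT criterion: a new ischaemic lesion on the follow-up NCCT 24–36 h after admission.
- MRI criterion: an ischaemic lesion on the MRI between the third and seventh day after admission.

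Every on-schedule scan then qualifies whatever the delay, because both the schedule and the limit are measured from admission. If the onset clock is kept instead, the limits would have to reach 24 + 36 = 60 h for NCCT and 7 + 1 = 8 days for MRI to cover the same scans.

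The cost is two wording changes. No scan is added or moved.

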## Introduction

Stroke mimics (SM) present a wide variety of neurological disorders that exhibit symptoms similar to those of a proven cerebrovascular accident (CVA—stroke), despite not being a true stroke. Every year, stroke affects approximately 28,000 people across the entire age spectrum in the Czech Republic, out of which one-third of patients succumb to the damage, some patients remain with a permanent deficit, and only a proportion of these patients recover fully from this disease. To achieve a positive outcome for patients with stroke, it is essential to initiate treatment early, which requires the early recognition of symptoms and the diagnosis of stroke. However, a rapid assessment can lead to the unintentional treatment of patients with SM, which is not indicated, is costly, and can lead to complications. A meta-analysis of data from 62,664 patients indicates that the average prevalence of SM is 24.8% (with an interval of 20–50%). The frequency of SM varies and depends on where the diagnosis is conducted and whether the patients are assessed by a physician at the emergency department or by a neurologist (1, 2).

SM can be divided into two main categories: medical SM and functional SM. Medical SM consist of brain disorders (migraine, seizures, posterior reversible encephalopathy syndrome/PRES, epidural/subdural haematomas, hypertensive encephalopathy, or brain tumours) and systemic diseases (electrolyte dysfunction and metabolic/toxic disorders). The frequency of the individual types of SM varies across different studies. The most recent comprehensive review showed the following frequencies of the different types of SM: peripheral vestibular syndrome 23.2%, toxic/metabolic disorders 13.2%, seizures 13%, migraine 7.8%, syncope 6%, mononeuropathy 5%, space-occupying brain lesions 4%, acute confusion 1.9%, dementia 1.2%, and spinal cord lesions 0.7% (3).

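### Read literally, the final-diagnosis rules class an intracerebral or subarachnoid haemorrhage as a stroke mimic, which contradicts the article's own concept of a mimic

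*Protocol article*

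**What the plan says.** **Stroke.** In Determination of the definitive diagnosis, the stroke rules open with "The following patients will be diagnosed with an ischaemic stroke". Three routes follow:
- "Patients with a finding of hypodensity corresponding with subacute ischaemia on the initial brain CT examination"
- "Patients with a new subacute ischaemic lesion on the follow-up NCCT scan within 36 h from the onset of the neurological deficit"
- "Patients with an ischaemic brain lesion on their MRI scan within 3–7 days from the onset of the neurological deficit"

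There is no rule for haemorrhagic stroke.

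**Stroke mimic.** The same section lists parameters for SM. The first is "organic lesion of aetiology other than ischaemic stroke on the NCCT scan". The second combines negative or discordant CTP with a negative control MRI. The third is independent confirmation by two neurologists and two radiologists, who weigh imaging against clinical data.

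**Entry and coding.** The inclusion criteria in Methods admit any acute neurological deficit with symptoms of up to 24 h. The exclusions listed there are age, prior severe handicap, contraindication to contrast CT or MRI, and non-consent. Table 1 ends with "in indicated patients stroke, stroke mimics". The first three words belong to the MRI item, and the remaining words are the two values of the final diagnosis.

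**Concept.** The Introduction describes mimics as conditions that look like stroke "despite not being a true stroke". Among bleeds, it names only epidural and subdural haematomas as mimics.

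**The concern.** The study's aim is the sensitivity and specificity of multimodal CT for SM versus stroke, so the final diagnosis is the reference standard for every accuracy table. A rule that sends haemorrhagic strokes to the SM side makes the target condition differ from the one the Introduction describes.

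The NCCT finding is also itself the reference criterion for these patients. NCCT would then be credited almost automatically with recognising them, although they say nothing about whether CTP helps to separate mimics from ischaemia. At stake are SM prevalence, sensitivity, PPV and NPV, the apparent increment from CTP described in the Discussion, and the make-up of the SM group in the outcome and cost summaries.

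**Working it through.** **Step 1: apply the written rules to a haemorrhage seen on NCCT.**

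| Rule | Met? |
|---|---|
| Not excluded by the listed criteria (Methods) | Yes |
| Hypodensity of subacute ischaemia on initial CT | No |
| New ischaemic lesion on follow-up NCCT | No |
| Ischaemic lesion on MRI | No |
| First SM parameter: non-ischaemic organic lesion on NCCT | Yes |
| A third final-diagnosis category (Table 1) | None exists |

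The SM list does not say whether its items are alternatives or must all hold. They cannot all hold, because CTP cannot be both negative and discordant in one patient. The workable reading is either imaging route, with panel confirmation on top. On that reading the only imaging rule a haemorrhage satisfies is an SM rule.

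**Step 2: compare with the pilot.** The article reports 37 mimics among 109 patients: 37/109 = 33.9%, stated as 34%. The rows of Table 3 sum to 7+5+3+3+3+2+1+1+1+1+10 = 37, with no row for haemorrhage.

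**Step 3: illustrate the size.** The article gives no haemorrhage share, so 5%, 10% and 15% of strokes are assumptions. A further assumption is that the 34% SM share contains no haemorrhage. With N = 3,000 (Statistic analysis):
- mimics = 0.34 × 3,000 = 1,020, and strokes = 0.66 × 3,000 = 1,980
- haemorrhages H = share × 1,980
- haemorrhage share of the SM group = H/(1,020 + H)
- SM prevalence under the literal rule = (1,020 + H)/3,000

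| Assumed share of strokes | H | Share of SM group | SM prevalence |
|---|---|---|---|
| 5% | 99 | 99/1,119 = 8.8% | 37.3% |
| 10% | 198 | 198/1,218 = 16.3% | 40.6% |
| 15% | 297 | 297/1,317 = 22.6% | 43.9% |

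The meta-analytic SM prevalence of 24.8% cited in the Introduction gives 744 mimics and 2,256 strokes. The shares become 13.2%, 23.3% and 31.3%.

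**Step 4: effect on accuracy.** Suppose NCCT flags every haemorrhage and the index reading counts it as SM. Sensitivity for SM then moves from s to (s × 1,020 + H)/(1,020 + H). With an assumed s = 10%, it becomes 201/1,119 = 18.0%, 300/1,218 = 24.6% or 399/1,317 = 30.3%. These patients move from true negatives to true positives, so PPV rises and NPV falls.

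NCCT is part of every strategy compared, so a haemorrhage is read alike under each. It adds the same count to every numerator, and the difference in sensitivity is multiplied by 1,020/(1,020 + H) = 0.912, 0.837 or 0.774. An assumed gain of 20 percentage points from CTP would appear as 18.2, 16.7 or 15.5 points.

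**The case against.** The strongest reply is that the rule is not applied mechanically. Two neurologists and two radiologists must confirm each SM diagnosis, and the Introduction's concept would lead them to call a haemorrhage a stroke. Table 1 codes stroke, not ischaemic stroke, so a place for it exists. The article is condensed: the STARD diagram is not shown, the clinical data checklist is only referred to, and either could deal with haemorrhage.

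The pilot points the same way. If 10% of strokes were haemorrhagic and all were sent to SM, the chance of none among 72 strokes would be 0.9^72 = 0.0005 (0.95^72 = 0.025 at 5%). Haemorrhages were therefore probably counted as stroke, or were not in the pilot cohort.

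This stands as a limit on what can be claimed about practice. It does not repair the text. The panel has no instruction on haemorrhage, and the one written parameter that fits points to SM. If the pilot counted haemorrhage as stroke, its 34% rests on a different definition from the one now written.

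A reader might infer more: that haemorrhages do enter the SM group, that they are a known and sizeable fraction, or that the rule could produce a false claim for CTP. The documents support none of these. Entry is not shown and the fraction is not given. Because NCCT is in every strategy, haemorrhages are concordant pairs. They leave the discordant counts unchanged and shrink the absolute increment, which works against the study's hypothesis. Nor does the text show that haemorrhages seen on NCCT would add to the claimed savings, which are built on the cost of thrombolysis.

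**Conclusion.** The point holds as a contradiction in the stated reference standard. Taken at their word, the final-diagnosis rules place intracerebral and subarachnoid haemorrhage with the mimics, while the Introduction says that mimics are not strokes. This takes haemorrhage to be a stroke in the ordinary sense of the word; the article does not say so in terms.

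If the rule is followed, prevalence, sensitivity for SM and predictive values are distorted and the absolute CTP increment is understated. On the illustrative assumptions, haemorrhages form 9–23% of the SM group and the increment shrinks by the same proportion. These are not estimates for this trial. The direction of the sensitivity shift also assumes that index readings treat a haemorrhage as SM; if they call it stroke, sensitivity falls instead. The shrinkage of the increment holds either way, provided each strategy reads the haemorrhage alike.

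**What to change.** Reconcile the Introduction, Table 1 and Determination of the definitive diagnosis:
- Add intracerebral or subarachnoid haemorrhage as a separate final-diagnosis code, counted as stroke.
- Reword the first SM parameter so that its exception covers haemorrhagic as well as ischaemic stroke.
- State which definition the pilot's 34% used.

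Keep the accuracy analysis in all consecutive patients with suspected stroke. As an optional supplement, report the CTP increment in patients without haemorrhage on the initial NCCT, where the added scan can still change the classification.

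The cost is one line in the criteria and one extra code. No new data are needed. The optional analysis would have somewhat fewer patients.

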### Analyse of CT and MRI examination

The results of NCCT, CTA, and CTP will be evaluated by a blinded radiologist against the clinical diagnosis and will then be compared with the multimodal CT examination evaluated by AI. The concordance of a positive CTP finding in relation to the clinic will be assessed by a specialist stroke neurologist. The AI software (e-Stroke, Brainomix, Oxford) provides a fully automated scoring tool for analysing CT and MRI examinations. The software calculates e-ASPECT and the volume of ischaemia; it analyses CTP and the values of collateral circulation. Furthermore, it can determine the area of vascular occlusion and the size of ischaemia on MRI. In this respect, Brainomix e-STROKE software is a unique and irreplaceable tool.

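### Alternative CTP cut-offs are read by the radiologists who confirm stroke mimics, in the same step, so accuracy at those cut-offs may be biased

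*Protocol article*

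**What the plan says.** Four places in the Protocol article bear on this.

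- **Multimodal CT** gives the limits used by the AI software: core as "decrease in CBF below 30% of the reference bilateral value" and "penumbra (prolongation of Tmax over 6 s". These define tissue states. They are not expressly named as the rule that makes a CTP positive for stroke versus SM.
- **Analyse of CT and MRI examination** sets out the index reading: "The results of NCCT, CTA, and CTP will be evaluated by a blinded radiologist against the clinical diagnosis", followed by comparison with the AI result. A stroke neurologist then judges whether a positive CTP fits the clinical picture. **MRI examination** defines discordance as hypoperfusion in a place that does not match the symptoms.
- **Determination of the definitive diagnosis** lists among the SM parameters "negative CTP, discordant CTP, and negative control brain MRI". Two neurologists and two radiologists "will confirm the diagnosis of SM independently, considering the correlation of imaging and clinical data (see clinical data checklist"). The next sentence adds the task in question: "The radiologists will also assess other thresholds during the CTP examination than the classically established ones (e.g., T max less than 6 s"). The section closes by having the two stroke consultants make the final diagnosis both aware and unaware of CTP. It says nothing similar for the radiologists.
- **Statistic analysis** promises accuracy, sensitivity, specificity and predictive values, without tying them to a CTP cut-off.

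**The concern.** Sensitivity and specificity describe a fixed rule, read without knowledge of the answer and judged against a diagnosis that the reading did not help to form. The alternative cut-offs are placed where both conditions are at risk.

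First, the radiologists who assess them are by position the adjudicators, who weigh imaging against clinical data. A borderline perfusion map may be read differently by someone who already thinks the patient had a seizure (review bias).

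Second, negative or discordant CTP is itself part of the route to SM. A patient whose Tmax delay lies between a lower cut-off and 6 s is CTP-negative at 6 s and CTP-positive at the lower cut-off. If the adjudicators look at both while deciding on SM, the reading can move the reference diagnosis as well as the test result, and pull the two towards agreement (incorporation bias).

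The Discussion rests the project's outcome on the combination with CTP being superior to NCCT alone or NCCT with CTA. Only the combination containing CTP has these extra cut-offs, so a bias of this kind would tend to favour the project's hypothesis.

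**Working it through.** The article reports no CTP sensitivity or specificity at any cut-off, so there is no figure of its own to reproduce here. The stated minimum of 718 patients does not depend on the cut-off. The first step is a reading of the text. The other two are illustrations with assumed accuracies.

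**1. Who reads the extra cut-offs, and with what information**

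| Item | Index reading | Extra cut-offs |
|---|---|---|
| Section | Analyse of CT and MRI examination | Determination of the definitive diagnosis |
| Reader | One blinded radiologist, then AI | The radiologists, directly after the two who confirm SM |
| Information | Blinded | "considering the correlation of imaging and clinical data" |
| CTP part of the diagnosis being made? | Not applicable | Yes, on the SM side |
| Assessed with and without CTP? | Not applicable | Stroke consultants only |

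That the adjudicators use clinical data is stated. That they are unblinded when reading the extra cut-offs is an inference from this, and a fair one.

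**2. One best cut-off chosen for everybody**

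Assumptions: normally distributed test values one SD wide, separation of 1.0 or 1.5 SD between stroke and SM, 34% SM (the pilot proportion), five candidate cut-offs, 2,000 simulated studies. Optimism is the apparent Youden index (sensitivity + specificity − 1) minus the true index at the chosen cut-off.

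| N | Optimism |
|---|---|
| 109 (pilot size) | 0.051 to 0.055 |
| 718 | 0.012 to 0.015 |
| 3,000 | 0.002 to 0.004 |

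At the planned size, data-driven choice of a common cut-off is not a material problem.

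**3. The cut-off allowed to differ between patients**

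Inputs: 3,000 patients with 34% SM gives 1,020 SM and 1,980 strokes. Assumed sensitivity and specificity are 0.70 and 0.90 at 6 s, and 0.85 and 0.75 at a lower cut-off.

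- 6 s for all: (0.70 × 1,980 + 0.90 × 1,020) / 3,000 = 0.768
- Lower cut-off for all: (0.85 × 1,980 + 0.75 × 1,020) / 3,000 = 0.816
- Best side for each patient: (0.85 × 1,980 + 0.90 × 1,020) / 3,000 = 0.867

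The last line needs the reader's clinical suspicion to be right in every patient. Let suspicion be right with probability a, independent of CTP given the disease:

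accuracy = 0.66 × (0.70 + 0.15a) + 0.34 × (0.75 + 0.15a) = 0.717 + 0.15a

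| a | Accuracy | Gain over 0.816 |
|---|---|---|
| 0.66 | 0.816 | none |
| 0.75 | 0.830 | 1.4 points |
| 0.80 | 0.837 | 2.1 points |
| 1.00 | 0.867 | 5.1 points |

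Three other assumed pairs of cut-offs, also with suspicion always right, give an excess over the better single cut-off of 3.4 (80.0% against 76.6%), 8.5 (85.0% against 76.5%) and 13.6 points (90.0% against 76.4%). All of these are ceilings.

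**The case against.** A reader might infer that the cut-off is freely movable and that CTP will be credited with an accuracy no single cut-off has. The article does not support that. It says the radiologists will also assess other cut-offs, which reads most naturally as an additional, perhaps exploratory, look beside the established limits. Multimodal CT and the Discussion both make 6 s the evident default. Nothing plans a different cut-off for each patient, and the figures for such switching are upper bounds that vanish when clinical suspicion is only moderately good. This part of the objection stands.

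It can also be said that the accuracy results may come only from the blinded and AI readings, which would leave the adjudicators' readings harmless to the main result. That is possible, but the article does not say it. Nor does it say where the results at the extra cut-offs will be used.

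On the reference side, the criteria for ischaemic stroke use lesions on CT or MRI and no CTP cut-off, and the consultants' double assessment offers some protection. This limits the incorporation problem to the SM side but does not remove it, because the radiologists are outside that safeguard.

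Finally, the absence of a named primary cut-off and of a list of alternatives would, on its own, be detail that a condensed article may leave to the full protocol or SAP. That is granted. Who reads the extra cut-offs, at which step and with what information is study conduct, and the article does set it. A later SAP cannot undo a reference diagnosis that such readings have already influenced.

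The literal wording of the example (Tmax below 6 s, which would include normal tissue) is a matter of language. A cut-off set lower than 6 s is evidently meant.

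**Conclusion.** The point holds in a limited form. Followed as written, the plan places the alternative cut-offs with readers who use clinical data, in a step where CTP helps to decide SM. Accuracy reported at those cut-offs could be biased by clinical knowledge and by entry into the reference diagnosis.

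The size cannot be computed from the document. Selecting one best cut-off for all 3,000 patients would add under 0.005 to the Youden index under the assumptions shown. Case-by-case switching could add more, but it is neither planned nor excluded and should not be presented as what the trial will do.

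The conclusion rests on taking the radiologists in the cut-off sentence to be the two named immediately before it. This is a cheap improvement, not a flaw that threatens the main reading at 6 s.

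**What to change.** 1. Name Tmax over 6 s (already in Multimodal CT), together with the existing concordance assessment, as the positivity rule for the main CTP accuracy result. The concordance step must stay, because the protocol treats hypoperfusion in the wrong place as discordant, not as support for stroke.
2. List the lower cut-offs in advance, each written as Tmax greater than a stated value.
3. Apply each to every patient in the blinded and AI reading described under Analyse of CT and MRI examination, before clinical or follow-up data are seen.
4. Report each as secondary, with its own sensitivity and specificity pair, and do not combine figures from different cut-offs.
5. Remove the cut-off sentence from Determination of the definitive diagnosis and keep these readings from the adjudicators.

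The cost is protocol wording and a change in the order of reading. No scans or patients are added, and the AI software already analyses CTP. The small downside is that a better cut-off found in these data would be reported as exploratory.
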